### Statistical analysis

For the analysis of the primary endpoint (feasibility and completion rate), we will estimate the probability of completion using the Binomial Fisher’s Exact Test, assuming individuals across centers are independent. Letting *P* be the probability of successful completion (week 6), we will reject the null hypothesis that *P*_(completion)_ ≤ 0.5. A confidence interval for *P*_(completion)_ will be estimated. In a second step, we will estimate the confidence intervals for each of the treatment arms separately.

The analysis of the secondary endpoint (efficacy) consists of an intention-to-treat (ITT) analysis of the change in MADRS scores from baseline to post-intervention by adjusting for inter-individual differences at baseline, sex, and center. A linear mixed regression model (LMM) with random intercepts and center, group, time, and the cross-level group x time interaction as fixed effects will be performed. The key value for significance will be the group × time interaction factor. In case of significant group × time interactions, post-hoc comparisons at each time point with correction of the type-I error probability will be conducted. Confidence intervals for mean differences and effect sizes will be computed. If the analysis at week 6 is found to be significant, an analysis of change over 10 weeks will be performed as a final analysis step concerning the secondary endpoint. All tertiary endpoints will be similarly analyzed using LMMs. Logistic regression will be used to analyze discrete tertiary endpoints (i.e., response and remission rates).

There will be no imputation in the ITT analyzes as the LMMs can handle missing values without excluding entire cases from the analysis. As a sensitivity analysis, LMMs can be computed using state-of-the-art multiple imputation of missing values. At 50% of subjects having completed the study, a planned interim analysis will assess safety and feasibility outcomes. The respective results will be shared with our SMB and published, but will not impact on the conduct of the study, unless major ethical concerns arise.

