### Study endpoints

The *primary* endpoint of the study is the *feasibility* of the combined intervention as assessed at the post-intervention visit (V4), except in case of compensation sessions, where *feasibility* will be assessed at the end of treatment. To test *feasibility*, we use the following quantitative definition: the intervention is feasible if the probability of a study participant to successfully apply a number of at least 20 out of 30 sessions per protocol exceeds 50%, i.e., it is more likely to receive an adequate dosage of treatment sessions. The threshold of 20 out of 30 treatment sessions is largely based on previous trials of tDCS in MDD, i.e., being close to the tDCS session number in the ELECT TDCS trial and at a higher number of sessions compared to the SELECT trial (22 sessions and 12 sessions, respectively; [26, 27]) to prevent an insufficient dosage of the intervention in this trial. To test this hypothesis, we will determine the quotient of participants successfully completing the intervention according to this criterion relative to the total number of participants. This endpoint was chosen as the primary endpoint due to the novelty of our study design, in which the treatment is performed mostly in a home-based setting. The study has been powered to examine feasibility in the whole sample (i.e., both treatment arms together). In a second step we will estimate confidence intervals for each of the treatment arms separately.

The secondary endpoint is *efficacy,* measured as the change in *MADRS* scores from the baseline visit (V1) to the post-intervention visit (V4). Tertiary endpoints include *clinical response* (at least 50% reduction in the MADRS score from baseline), *remission rates* (MADRS score ≤ 10 points), and *depression relevant status,* assessed via changes in depressive and functional outcomes. Changes on all other assessments from baseline to post-treatment, including *QoL, rumination*, and *cognitive control functions* including *multitasking*, *inhibitory control* as well as *sustained attention* are also included as *tertiary* endpoints*.*

*Exploratory* endpoints include *durability of effects* (i.e., changes on all measures between baseline and follow-up), *expectation for treatment effects* (CEQ scale), *motivation* to participate in the game (IMI scale), and additional domains of cognitive control including the assessment of *WM capacity* and *task switching*.

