### Randomization and blinding

Participants are randomized to receive either active or control treatment following a parallel group assignment. Randomization is performed separately for each site. Patient allocation is stratified by the magnitude of the MADRS score (MADRS < 21.5 vs. MADRS ≥ 21.5). No other stratifiers are used to conserve statistical power. Within stratification, allocation is balanced in groups of four. Randomization is centrally performed by the coordinating site (HUJI) using an online randomization tool (Randomizer; https://www.randomizer.at).

Double-blinded treatment is implemented to minimize bias during the data assessment driven by potential expectation biases of raters and/or patients. Separate study personnel are responsible for the study assessments (*raters, i.e., blinded investigators*) as compared to the implementation and supervision of the treatment (*unblinded investigators* including *study operators*). Raters and patients are blind to the administered treatment condition. Raters are not in direct contact with the patients during the treatment sessions. Patients are asked to refrain from talking about their treatment (apart from experienced AEs) with the raters. Study participants are required to refrain from meeting each other before, during, and after assessments or treatments to maintain blindness. A *blinding check* is performed after the first treatment and after six weeks of intervention (V4), in which patients are asked whether they believe that they were assigned to the active or to the control condition.

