### Sample size calculation

Sample size was determined based on the feasibility analysis (primary endpoint). Our primary hypothesis that the probability of completion is larger than 0.5 will be tested using a one-sided binomial test. Assuming *N* = 114 subjects, the one-sided binomial test would reject the null hypothesis (i.e., that the probability of completion is equal or less than 0.5) if the number of completers is ≥ 65 patients. This would constitute an effective completion rate of 57%. In terms of power, if the true completion rate is instead 2/3 (0.67), the probability of rejecting the null hypothesis would amount to approximately 0.98.

This sample size would also adequately power the efficacy analyzes (i.e., time x treatment interaction effect for MADRS change). Power in this analysis was estimated using a Monte-Carlo simulation of 10,000 datasets. Setting the threshold for detection at a significance level of 0.05 (one-sided), the estimated power for *N* = 114 subjects (38 enrolled per site) is 1-β = 0.91. A drop-out rate of 20% was incorporated, based on a comparable ongoing trial at the LMU Munich site [46]. Power measured the probability of detecting a significant time × treatment interaction effect. Effects were estimated using a linear mixed regression model (LMM), with time × treatment and center as fixed effects and subjects modeled as random effects. In the Monte-Carlo simulation, it was assumed that the time × treatment interaction effect was 4 points on the MADRS scale (adapted from [85]). The random effects were set at SD = 6 points for individual change (beyond baseline variability) and a standard deviation of 2.5 points was added as a center × treatment × time interaction. The assumed effect size of the interaction, after controlling for baseline, was Cohen’s *d* of 0.41 (medium effect size).

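### The mixed model listed for MADRS change has no sex term and no baseline covariate, so it does not deliver the adjustment the article promises for its key efficacy test

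*Protocol article*

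**What the plan says.** All of this is in the protocol article.

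- **Study endpoints:** the secondary endpoint is efficacy, "measured as the change in" MADRS from V1 to V4.
- **Statistical analysis, the promise:** the intention-to-treat analysis of that change is to be done "by adjusting for inter-individual differences at baseline, sex, and center".
- **Statistical analysis, the model:** the next sentence specifies a linear mixed model "with random intercepts and center, group, time, and the cross-level group x time interaction as fixed effects". The decision rule follows: "The key value for significance will be the group × time interaction factor".
- **Randomization and blinding:** "Patient allocation is stratified by the magnitude of the MADRS score", with a cut at 21.5, separately by site.
- **Sample size calculation:** the model used for power has time × treatment and center as fixed effects and subjects as random effects, again without a baseline or sex term. Yet the text continues: "The assumed effect size of the interaction, after controlling for baseline, was" d = 0.41.

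**The concern.** Of the three adjustments promised, only center appears among the listed terms. This is not detail left to a fuller document: the article names the terms, and they disagree with the sentence just before.

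Adding the missing covariates looks like an easy repair, but it may not work. The test is an interaction with time, and V1 seems to be one of the time points. A covariate that is constant within a patient and enters only as a main effect cannot act on that interaction. An analyst could then report an adjusted test that is numerically the unadjusted one. Another analyst could fit a true baseline-adjusted model, obtain a different estimate, and also claim to have followed the plan.

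This is the trial's main efficacy test. Its result decides whether the 10-week analysis is done, and the tertiary endpoints are to be analyzed in a similar way.

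**Working it through.** **1. The plan's own power figure.** Inputs from Sample size calculation: effect 4 points, SD of individual change 6, additional SD 2.5, N = 114, 20% dropout. The test level is "Setting the threshold for detection at a significance level of 0.05 (one-sided"), and the stated result for 114 is "subjects (38 enrolled per site) is 1-β = 0.91". Assuming 1:1 allocation, 57 × 0.8 = 45.6 per arm remain. Treating the 2.5 as patient-level variance, SD = √(6² + 2.5²) = 6.5.

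- SE = 6.5 × √(2/45.6) = 1.361
- Power = Φ(4/1.361 − 1.645) = Φ(1.293) = 0.902

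This agrees closely with 0.91 and is the starting point below. If the 2.5 is instead a random shift of the treatment effect between centers, average power is about 0.79 to 0.85.

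**2. What the listed interaction estimates.** With complete data, V1 among the outcomes and time categorical, group × time is saturated. The V4 interaction is then

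(mean V4 − mean V1) in the active arm − (mean V4 − mean V1) in the control arm.

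The random intercept cancels within each patient. So does any main effect that is constant over time, such as center, sex or a baseline covariate.

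**3. Numerical check.** 40 complete data sets were simulated with 114 patients in three centers and four visits. Assumed values were SD 6, correlation 0.5 between visits, a 4-point effect at V4 and a 2-point sex effect.

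| Model | V4 treatment contrast | Mean SE |
|---|---|---|
| Listed mixed model | equals raw change-score difference (largest gap about 1e-13) | 1.113 |
| Listed model plus sex and baseline main effects | same estimate | 1.113 |
| V4 regressed on baseline, sex, center and group | different estimate | 0.968 |

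The variance ratio of the last row to the first is (0.968/1.113)² = 0.756; theory gives 0.75. In the first four data sets the baseline-adjusted and listed-model estimates differed by 0.04, 0.45, 0.38 and 0.73 points, so the choice of model matters for the result.

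**4. Size of the possible gain.** Let ρ be the V1–V4 correlation and k the ratio of the V4 SD to the baseline SD. The documents give neither, so both are assumptions here.

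Var(adjusted)/Var(change) = k²(1 − ρ²)/(1 + k² − 2ρk), which is (1 + ρ)/2 when k = 1.

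Power holds the change SD at 6.5 with 45.6 per arm, one-sided 0.05, starting from 0.902:

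| ρ | k = 1: ratio | k = 1: power | k = 1.5: ratio | k = 1.5: power |
|---|---|---|---|---|
| 0.3 | 0.65 | 0.977 | 0.87 | 0.934 |
| 0.5 | 0.75 | 0.960 | 0.96 | 0.911 |
| 0.7 | 0.85 | 0.939 | 1.00 | 0.903 |

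If change is independent of baseline, then ρ = 1/k. The ratio becomes (k² − 1)/(k² − 1) = 1, and nothing is gained.

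**The case against.** The strongest reply is that the article commits in words to adjustment, the term list may be abbreviated, and random intercepts may be what was meant by differences between individuals at baseline. Part of this stands. A reader might infer that the trial plans an unadjusted change-score analysis; the documents do not support that, because one sentence promises the opposite. What they show is a contradiction. The random-intercept reading does not rescue the model, however, since the intercept leaves the V4 contrast untouched.

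A second reply is that the exact equality needs complete data and categorical time. The article expects 20% dropout and does not say how time is coded. This is correct: with missing V4 values the equality is not exact. But nothing in the listed terms then supplies a regression on baseline.

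A third reply concerns precision. A reader might infer that the listed model plainly wastes precision, or costs 15% to 35% of the patients. That range needs equal variances and an assumed ρ. The entry threshold of HDRS-17 ≥ 13 truncates baseline severity, so a wider V4 spread is plausible. The sample size section describes the SD of 6 as coming on top of baseline variability, and one reading of that is change independent of baseline, with no gain at all. Nor should a gain be added to d = 0.41: the article describes that d as already controlled for baseline, so the adjustment would be counted twice. N was in any case set on feasibility.

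Finally, no sentence promises a term for the MADRS stratum, so its absence contradicts nothing. Stratified blocks of four also limit gross baseline imbalance, though not imbalance within strata.

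**Conclusion.** The point holds as a contradiction with a practical consequence. The listed model lacks two of the three promised adjustments. Under categorical time and complete data, its key test is the raw change-score difference, and adding baseline and sex as main effects would not change that.

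The size of the loss is open. Over the assumptions shown, the variance reduction available runs from 0 to about 35%, and power would move from about 0.90 to between 0.90 and 0.98. These power figures rest on a change SD of 6.5, 45.6 per arm and a one-sided 0.05 test. The documents do not say where in that range the trial lies.

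This concerns the secondary endpoint and does not affect the feasibility analysis. It should be corrected, chiefly so that only one model satisfies the plan.

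**What to change.** State one model, in one of two forms:

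- **Baseline as covariate:** MADRS at V2–V4 as outcomes, with continuous baseline MADRS, baseline × visit, sex, center, group, visit and group × visit. The test is the group contrast at V4, not an interaction with V1.
- **Baseline as outcome:** MADRS at V1–V4 as outcomes, with a common V1 mean across arms, plus center, sex and sex × visit. The test is again the group difference at V4.

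Reword the decision rule to name that contrast, and say that time is categorical. The MADRS randomization stratum may be added, but continuous baseline MADRS largely covers it. Align the sample size section by saying what controlling for baseline meant in the power model, since that model lists no baseline term.

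The cost is wording only, because MADRS, sex and center are already collected. In large samples, linear adjustment for baseline is no less precise than the change score, so precision gives no reason against the change.

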## Trial design and methods

### Trial design

The DiSCoVeR clinical trial is a multi-center, two-arm, double-blind, randomized controlled trial (RCT), conducted at three clinical sites (Hadassah Medical Center, Israel; Riga Stradins University, Latvia; Ludwig-Maximilians-University, Germany). The goal of the trial is to examine the feasibility and safety, as well as, secondarily, the efficacy of a combined treatment approach (tDCS + LoH video game) with components that have been developed and integrated in the preceding phases of the DiSCoVeR project.

*Study visits* are scheduled for screening (V0) and at baseline (V1), at two time points during the intervention (week 2, V2; week 4, V3), at week 6 upon completion of the intervention (V4), and at week 10 at follow-up (V5) (Fig. 1). All patients are required to provide written informed consent prior to participating in any study-related procedures. During the *screening phase,* patients are evaluated for study eligibility based on the inclusion and exclusion criteria described below. Eligible patients are randomly assigned to one of two study arms: (A) active condition (active tDCS + LoH game) or (B) control condition (sham tDCS + LoH_control game). In the *baseline phase*, data are obtained using clinical rating scales, self-rating questionnaires, and CC tasks.

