### Study assessments

*Feasibility* is continuously assessed during the intervention phase. After each treatment session, it is recorded whether the session has been completed successfully. Reasons for interruptions, discontinuation, and potential restarts of the device are also carefully documented.

*Depression severity* as a study endpoint is measured using the *MADRS* [60]. From the baseline visit (V1) to the follow-up visit (V5), the clinician-based MADRS rating is complemented by self-assessment measures of depressive symptoms including the *Beck Depression Inventory* (*BDI-II*; [71]) and the *Patient Health Questionnaire*; (*PHQ-9* [72]*;*). We additionally assess anxiety using the *Generalized Anxiety Disorder 7-item* (*GAD-7*; [73]) and trait rumination using the *Rumination Response Scale* (*RRS*; [74]).

Patients are rated for their global severity of illness (*Clinical Global Impression-Severity; CGI-S*; [75]) and its change over time (*Clinical Global Impression-Improvement; CGI-I*; [75]). Quality of life (QoL) based on aspects of *positive mood*, *vitality,* and *general interes*t is assessed using the *WHO-5 well-being index* [76]. Patients’ social, occupational, and psychological functioning in their daily life is rated using the *Global Assessment of Functioning Scale* (*GAF*; [77]).

CC functions are measured behaviorally across a wide range of neuropsychological domains using the computerized *Adaptive Cognitive Evaluation* (*ACE*) *battery* [78]. The ACE battery includes standardized tests for different aspects of CC, modified by incorporating adaptive algorithms, immersive graphics, video tutorials, and motivating feedback on a user-friendly interface. Adaptive algorithms ensure that comparisons between individuals of different age groups, genders, races, and cultures reflect actual differences in their cognitive ability and not disparities in the testing parameters or ceiling/floor effects. In the context of the DiSCoVeR trial, we assess the following CC functions: *inhibitory control*, *task switching*, *multitasking*, *impulsivity*, *sustained attention*, and *working memory capacity*.

Intrinsic motivation for game play and expectancy of treatment outcome are assessed after the fifth session on site and at post-intervention using the *Intrinsic Motivation Inventory* (*IMI*; [79, 80]) and the *Credibility/Expectancy Questionnaire* (*CEQ* [81]*;*).

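### The efficacy mixed model has random intercepts only and is judged by the group × time factor; if V2 and V3 enter it, the test is either anti-conservative or not specific to the V1-to-V4 endpoint

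*Protocol article*

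**What the plan says.** All references are to the protocol article.

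- **Model** (Statistical analysis): "A linear mixed regression model (LMM) with random intercepts and center, group, time, and the cross-level group x time interaction as fixed effects". No random effect for time and no other within-patient covariance is given.
- **Decision rule** (same section): "The key value for significance will be the group × time interaction factor". After a significant interaction, "post-hoc comparisons at each time point with correction of the type-I error probability will be conducted". The same section describes the target as change from baseline to post-intervention and speaks of the analysis at week 6, with change over 10 weeks as a later step.
- **Endpoint** (Study endpoints): the change in MADRS "scores from the baseline visit (V1) to the post-intervention visit (V4").
- **Visits** (Trial design): after baseline, "at two time points during the intervention (week 2, V2; week 4, V3), at week 6 upon completion of the intervention (V4"), then follow-up at week 10. Study assessments adds: "From the baseline visit (V1) to the follow-up visit (V5), the clinician-based MADRS rating is complemented by self-assessment measures of depressive symptoms".
- **Power** (Sample size calculation): a 4-point interaction effect, one-sided 0.05, N = 114, 20% drop-out, power 0.91. The random effects are an SD of 6 "points for individual change (beyond baseline variability") and an SD of 2.5 for center × treatment × time. Subjects are random effects, but whether as intercepts or slopes is not said.

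The article does not say which visits enter the efficacy model, whether time is linear or categorical, or what the residual SD is.

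**The concern.** There are two separate issues, and which one applies depends on how the model is read.

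**Variance.** If patients truly differ in their change, their deviations from baseline are correlated across visits and grow with time. A random-intercept model forces equal correlation and constant variance, so it treats person-specific change as independent residual noise. With more than two visits, the standard error of a slope or of a V4-versus-V1 contrast is then too small.

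**Target.** The endpoint and the power calculation concern one directional contrast. With four visits (V1 to V4) and categorical time, the group × time factor is a 3-df, non-directional test. With linear time it tests a slope, not the V4 difference.

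This test decides the efficacy claim and gates the 10-week analysis. The tertiary endpoints are to be analyzed similarly.

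**Working it through.** **1. The plan's own power.** Inputs from the sample size section: 57 per arm × 0.8 = 45.6 (assuming 1:1 allocation), effect 4, SD √(6² + 2.5²) = 6.5. SE = 6.5 × √(2/45.6) = 1.361. Power = Φ(4/1.361 − 1.645) = Φ(1.293) = 0.902, close to the stated 0.91. The figure therefore fits one change score tested one-sided.

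**2. Standard error with four visits.** Assumptions not in the article: V1 to V4 at t = 0, 1/3, 2/3, 1; individual change b·t with SD(b) = 6; independent residuals with SD s; complete data.

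- Σ(t − t̄)² = 0.5556, so the least-squares slope of one patient has true variance 36 + s²/0.5556 = 36 + 1.8s².
- A random-intercept model pools the within-patient variation into one residual variance: (36 × 0.5556 + 3s²)/3 = 6.67 + s².
- Linear time: the model uses 1.8 × (6.67 + s²) = 12 + 1.8s², where 36 + 1.8s² is true.
- V4-versus-V1 contrast: the model uses 2 × (6.67 + s²) = 13.3 + 2s², where 36 + 2s² is true.

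With r = √(model variance / true variance), the two-sided error is 2[1 − Φ(1.96r)] and the one-sided error is 1 − Φ(1.645r).

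| s | slope: r | two-sided | one-sided | V4 contrast: r | two-sided | one-sided |
|---|---|---|---|---|---|---|
| 2 | 0.667 | 0.191 | 0.136 | 0.696 | 0.172 | 0.126 |
| 3 | 0.735 | 0.150 | 0.113 | 0.762 | 0.135 | 0.105 |
| 4 | 0.793 | 0.120 | 0.096 | 0.816 | 0.110 | 0.090 |
| 5 | 0.839 | 0.100 | 0.084 | 0.858 | 0.093 | 0.079 |
| 6 | 0.873 | 0.087 | 0.076 | 0.889 | 0.081 | 0.072 |

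**3. Simulation** (114 patients, baseline SD 5 assumed, 0% and 20% drop-out, s from 6 down to 2, nominal two-sided 0.05, random intercepts only):

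- linear slope: 0.087 to 0.198;
- V4 contrast: 0.080 to 0.194, or 0.07 to 0.13 if individual change is a constant shift after baseline instead of linear growth;
- 3-df factor: 0.043 to 0.094;
- V1 and V4 only (tested on change scores): 0.046 to 0.051.

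A REML cross-check (s = 3, 20% drop-out, 150 runs) gave 0.187 for linear time with random intercepts and 0.067 with a random slope added (Monte Carlo SE of the latter about 0.02).

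**4. What the 3-df factor responds to.** With a group difference of 4 points at V2, 2 at V3 and 0 at V4 (complete data), the factor was significant in 99% of runs at s = 3 and 93% at s = 4. A test of V1-to-V4 change stayed at 5.4% to 5.5%.

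**5. Power for a 4-point V4 effect** (linear growth, 20% drop-out). The 3-df factor in the random-intercept model: 0.88, 0.79, 0.68 and 0.50 at s = 2, 3, 4 and 5. Part of that shortfall from 0.91 comes from the assumed residual SD, so the fair comparison holds s fixed and uses the correct covariance:

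| s | V4 contrast, one-sided 0.05 | 3-df factor |
|---|---|---|
| 2 | 0.92 | 0.73 |
| 3 | 0.86 | 0.63 |
| 4 | 0.77 | 0.52 |

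**The case against.** The strongest reply is that the article never says V2 and V3 enter the model. It describes change from baseline to post-intervention and the analysis at week 6, and the stated power is reproduced by a single change score. With V1 and V4 only, a random intercept carries the change variance exactly and the interaction is the endpoint. This stands: on that reading there is no defect. But comparisons at each time point, with correction for multiplicity, make little sense with one post-baseline visit, and V2 and V3 are scheduled. The multi-visit reading is the more natural one.

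Second, reading the SD of 6 as a random slope is an inference. If it is the total SD of V1-to-V4 change, a random-intercept model with residual SD 6/√2 = 4.24 fits it, and four-visit simulations then gave an error of 0.041 to 0.053. This also stands as a condition on the inflation, though listing the 6 among the random effects and setting it beyond baseline variability favors the person-level reading.

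Third, a reader might infer that the V4 endpoint goes untested. The article does not support that: a significant interaction is followed by corrected comparisons at each time point and confidence intervals for mean differences, so a V2-only effect would be located at V2. What remains is that V4 is reached only through an omnibus gate, which costs power, and that significance itself is assigned to the factor.

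Fourth, the visits, the coding of time and the named contrast are often left to an analysis plan, which is not shown. The point therefore rests on what the article does fix: the random-effects structure and the decision rule.

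**Conclusion.** The point holds conditionally. If V2 and V3 enter the model and the SD of 6 is person-specific change beyond residual noise, a slope or V4 test is anti-conservative, at about 0.08 to 0.20 for nominal two-sided 0.05 (assumed residual SD 6 to 2). If instead the 3-df factor is the test, its error is near nominal, and the fault is a non-directional, less powerful test that does not isolate V4.

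It is tempting to conclude that the efficacy error rate is simply wrong under the trial's own variance assumptions. The article does not support that. The clear inflation and the omnibus factor belong to different readings, the residual SD, baseline SD and shape of change are assumed here, and a V1-and-V4 model is sound. This should be fixed, but it is not critical: efficacy is the secondary endpoint, and the primary feasibility analysis is untouched.

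**What to change.** Before unblinding, amend the efficacy paragraph to:

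- state which visits enter the model, and code time as categorical;
- name the group difference in MADRS change from V1 to V4 as the single efficacy test, with estimate, confidence interval and p value, not gated by the omnibus interaction;
- use an unstructured within-patient covariance, with random intercept plus random slope as the fallback;
- report V2 and V3 comparisons as descriptive.

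Apply the same covariance to the tertiary endpoints analyzed by mixed models. The cost is a wording change and a few more covariance parameters, which is minor at N = 114. No new data or patients are needed.

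### Center enters the MADRS model only as a main effect, so the promised center adjustment does not reach the group × time test; the cost is some precision

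*Protocol article*

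**What the plan says.** The Statistical analysis section describes the secondary efficacy analysis as an intention-to-treat analysis of the "change in MADRS scores from baseline to post-intervention by adjusting for inter-individual differences at baseline, sex, and center". The next sentence fixes the model, a linear mixed model with random intercepts and "center, group, time, and the cross-level group x time interaction as fixed effects". The test is then named: "The key value for significance will be the group × time interaction factor".

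The model behind the power figure, under Sample size calculation, has the same structure: "with time × treatment and center as fixed effects and subjects modeled as random effects". Under Randomization and blinding, "Randomization is performed separately for each site", with allocation balanced in groups of four within MADRS strata.

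The Trial design section places visits at baseline (V1), week 2 (V2), week 4 (V3) and week 6 (V4). The article does not say which of these enter the efficacy model, or whether time is linear or categorical.

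**The concern.** A group × time term measures a treatment effect on change when baseline is one of the repeated outcome values. In that layout a center main effect describes how high MADRS scores run at a site. It says nothing about how much patients at that site improve. The stated aim (a change adjusted for center) and the listed terms therefore do not match.

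The site-wise randomization makes this relevant. Balancing the arms within each site removes shared site differences in improvement from the true sampling error of the treatment contrast. An analysis gets the benefit only if it also removes those differences from its residual. With three sites in three countries and concomitant psychotherapy allowed, some site difference in improvement is plausible. What is at stake is the width of the confidence interval and some power for the main efficacy comparison.

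**Working it through.** **1. The plan's own power figure.** Inputs from Sample size calculation: N = 114 (38 per site), effect 4 points, SD of individual change 6, center component SD 2.5, drop-out 20%, one-sided 5%, stated power 0.91.

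- Combined SD = √(6² + 2.5²) = 6.5.
- With 114 × 0.8 / 2 = 45.6 per arm: SE = 6.5 × √(2/45.6) = 1.361; power = Φ(4/1.361 − 1.645) = 0.902.
- With 57 / 1.2 = 47.5 per arm: SE = 6.5 × √(2/47.5) = 1.334; power = 0.912.

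The stated 0.91 is reproduced if the 2.5 points are treated as extra patient-level variance.

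**2. Why the center term cancels.** For patient i at center c in group g, write the listed model as

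Y(it) = α + γ(c) + βg + τ(t) + δ·g·t + u(i) + e(it).

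The V1-to-V4 change is τ + δg + [e(i4) − e(i1)]. Both γ(c) and u(i) have gone. Any site difference in improvement is left in the bracket. A center × time term adds κ(c) to the change and takes it out again.

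**3. Check by fitting the model.** SE of group × time from REML fits:

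| Data | No center | Center main effect | Center × time |
|---|---|---|---|
| One complete two-visit dataset, site SD 4 | 1.4423 | 1.4423 | 1.0656 |
| Mean of 40 complete two-visit datasets, site SD 2.5 | 1.190 | 1.190 | 1.118 |
| The same 40 with 20% drop-out | 1.285 | 1.283 | 1.213 |

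With complete data, adding the center main effect changed no estimate by more than 8 × 10⁻¹⁴. With drop-out it moved single estimates by up to 0.29 points but hardly changed the SE.

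**4. Size for a V1-to-V4 contrast.** Let s be the SD between sites in mean improvement common to both arms. The article does not give s, so a range is shown. For three equal sites the realised between-site variance averages (2/3)s², so

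- SE with center adjustment ≈ 6 × √(2/45.6) = 1.257;
- SE ratio without it ≈ √[(36 + (2/3)s²)/36].

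Simulated results are from 20,000 trials per value of s (20% random drop-out, effect 4, one-sided 5%):

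| s | Ratio by formula | SE, main effect only vs adjusted | Power, main effect only vs adjusted |
|---|---|---|---|
| 0 | 1.000 | adjustment costs 0.3% | 0.934 vs 0.932 |
| 1.25 | 1.014 | 1.27 vs 1.26 | 0.928 vs 0.931 |
| 2.5 | 1.056 | 1.33 vs 1.26 | 0.913 vs 0.928 |
| 4 | 1.139 | 1.42 vs 1.26 | 0.887 vs 0.932 |

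The value 1.25 is half of 2.5: the arm-averaged site shift if a 2.5-point site effect falls on the active arm alone. A separate run of 5,000 trials agreed: SE 1.328 vs 1.261 and power 0.922 vs 0.938 at s = 2.5; 1.428 vs 1.257 and 0.886 vs 0.933 at s = 4. One-sided size without the adjustment came out between 0.037 and 0.048 at s = 2.5 and between 0.035 and 0.038 at s = 4, depending on the run.

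**5. Four visits with random intercepts only.** Assumptions: V1 to V4, complete data, linear time, linear individual trajectories, SD of V1-to-V4 change 6. One-sided size at nominal 0.05, listed model vs center × time added:

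| Residual SD | s = 2.5 | s = 4 |
|---|---|---|
| 2 | 0.121 vs 0.132 | 0.102 vs 0.125 |
| 3 | 0.085 vs 0.092 | 0.079 vs 0.091 |
| 4 | 0.054 vs 0.057 | 0.045 vs 0.053 |

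Here random intercepts miss the patient-to-patient variation in slope. The SE is already too small in most cells, and center × time by itself shrinks it further.

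**The case against.** **The outcome layout is inferred.** The article nowhere says that baseline is an outcome row. Its first sentence speaks of change adjusted for baseline, and Sample size calculation also mentions controlling for baseline. If change or post-baseline score is the outcome, a center main effect does adjust it. This stands as a genuine ambiguity, and the point is conditional on the reading. The choice of group × time as the decisive term favors the repeated-measures reading: with post-baseline outcomes only, that term would test whether the arms diverge further between post-baseline visits, not the difference in change from baseline.

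**Details belong in the analysis plan.** Often so. Here, however, the article lists the fixed effects and names the test, so what it fixes can be compared with what it promises.

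**The direction depends on the model.** A reader might infer that the planned test is conservative throughout. That does not follow. Step 5 shows that with several visits and random intercepts only, the SE is often too small. The widening is established for a V1-to-V4 contrast.

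**The effect is small and the endpoint secondary.** This also stands. The sample size rests on feasibility, and power stays near 0.89 even at s = 4.

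**The protocol's own heterogeneity figure is a different quantity.** The 2.5 points under Sample size calculation are center × treatment × time, so they cannot be taken as the SD that drives this point. With SD 2.5 on that component, center × time does not help: power 0.832 vs 0.836, and rejection at zero average effect 0.129 vs 0.133.

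**Conclusion.** The mismatch holds on the natural reading of the listed model: center is named as an adjustment of the MADRS change, but in the form given it leaves the tested effect unadjusted. For a V1-to-V4 contrast the SE is about 5% too wide if sites differ in shared improvement with SD 2.5, and about 13% too wide at SD 4, where power is about 0.89 instead of 0.93. At SD 1.25 or less the loss is negligible. These figures rest on the protocol's N, effect, SD of change and drop-out, on balanced arms within sites, and on an assumed site SD that the article does not supply.

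A reader might go further and infer that unequal drop-out lets site differences bias the group × time estimate. Nothing in the article establishes such a pattern, and the calculations used random drop-out and near-balanced arms. The demonstrated cost is precision.

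**What to change.** In the Statistical analysis section, define the efficacy analysis as the V1-to-V4 MADRS change, or the post-baseline MADRS scores, with group as the treatment term and baseline MADRS and center as covariates. Take the group difference at V4 as the tested effect. This delivers the center adjustment already promised and uses the site-wise randomization. The post-baseline version sits better with the plan to let the mixed model handle missing values, because patients seen at V2 or V3 but not at V4 still contribute.

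If the repeated-measures model with baseline as an outcome is kept, add center × time, but only together with a covariance structure across V1 to V4 that does not rest on random intercepts alone, for example unstructured. Center × time by itself is not a safe repair (step 5). Carry the same choice into the mixed models for the tertiary endpoints and into the model under Sample size calculation.

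The cost is a sentence or two of wording and no new data: two degrees of freedom (two per post-baseline visit in the repeated-measures version), and about 0.2 percentage points of power if sites do not differ (0.934 vs 0.932). The center × treatment × time component in the power simulation needs its own treatment.
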